### Dashboard

The *Dashboard* section (Fig. 2) uses a traffic light system to provide participants with a visual representation of their progress toward achieving a predetermined standard level of each behaviour. These levels were selected based on guidelines or available evidence on the lowest risk of overall mortality or cardiovascular disease [1, 2, 48]. The traffic light colours change when the information entered in the *Your Stats* section is updated (user-entered group) or when the Fitbit is synchronised (device-entered group). Green reflects that a user’s behaviour meets or exceeds the predetermined standard. Orange reflects that a user’s behaviour somewhat lowers their risk, however more positive changes are needed. Red reflects that a participant’s behaviour is markedly below the predetermined standard and associated with significant health risk. The dashboard is intended to operationalise the construct of feedback on behaviour.

**Fig. 2 Fig2:**
[figure not shown]
Screenshot of the Balanced Dashboard displaying Orange, Red and Green feedback to the user on Activity, Sedentary and Sleep behaviours respectively

### Your stats

The *Your Stats* section (Fig. 3) allows participants to see time spent in moderate-to-vigorous intensity physical activity, time spent sedentary, time to sleep and time to wake, and sleep quality. The user-entered group used this section to enter data on each of these behaviours. In this section, participants can enter goals for all behaviours except sleep quality because individuals can engage in activities that can promote improved sleep quality (eg. sleep hygiene behaviours), but sleep quality is not directly under their control. Participants may also enter a subjective rating to indicate whether they believe their current behaviour is a risk to their health, using a dichotomous yes or no response format, in this section. This seeks to engage participants in evaluation of their behaviour, in relation to the information provided in the resources section and feedback provided by the traffic light system. It is intended to align their perceptions of their behaviour with their actual level of behaviour, as many people are likely to have misaligned perceptions of their lifestyle behaviours [49, 50]. The information entered in this section is intended to operationalise the constructs of goals setting and self-monitoring.

**Fig. 3 Fig3:**
[figure not shown]
Screenshot of Your Stats section for Activity

### Progress

The *Progress* section provides graphical feedback of behaviours in comparison to goals on duration of physical activity, sedentary behaviour and sleep, sleep quality, and the pattern of sleep (time to sleep and time to wake), using four time periods: daily, weekly, 3 month, and total usage period. The device-entered group are provided with graphs displaying summaries of the number of minutes spent in moderate-to-vigorous intensity physical activity, and in sedentary behaviour, in 15 min periods (See Fig. 4a). The manual-entered group receives daily summaries for these behaviours in the form of a single bar graph (See Fig. 4b). The sleep pattern graph shows the time to bed and time to wake, as consistency in these times is a key behavioural target for improving sleep quality (Fig. 4c) [12, 51, 52].

**Fig. 4 Fig4:**
[figure not shown]
**a** Daily summary graph of activity for the device-entered group. **b** Daily summary graph of activity for user-entered group. **c** Graph of time to sleep and time to wake over a 1 week period

### Resources

The *Resources* section provides information on the benefits of, and barriers to improving targeted health behaviours, and details of the criteria used to determine colours in the Traffic Light system on the Dashboard. Strategies to improve behaviours were adapted from our previous interventions and existing resources (i.e. National Guidelines, National Heart Foundation, Sleep Health Foundation), including goal setting strategies [28, 40, 51, 53, 54]. Sleep education materials will include sleep hygiene education information based on existing information [51, 53]. Education materials will promote the *formation of habits* around target behaviours (i.e. scheduling activities, creating routines around behaviours) to engrain behaviours in daily life and promote longer term changes [55]. These materials use an approach similar to that used in previous interventions, by providing concise information on each behaviour in a “Why”, “How”, and “How much” format [28]. The resources section is intended to operationalise the behaviour change techniques of education and action planning.

### My Profile

The *My Profile* section allowed participants to alter their email address, change their password and provided a description of the research team.

### Device-entered self-monitoring

Participants in the device-entered group will self-monitor physical activity, sedentary and sleep behaviour using data from the Fitbit. The Fitbit measures these behaviours and automatically synchronises with the Balanced platform using the Fitbit Application Programming Interface (API) (See Fig. 5) to display information on these behaviours in the Balanced platform. Participants will not be required to interact with the Fitbit website or app in anyway, furthermore they will be asked not to use these throughout the intervention. In the device-entered group, activity and sedentary behaviour are measured using steps per minute criteria of >100 steps and zero steps per minute respectively [56–58]. Time to sleep, time to wake and sleep quality (derived from the ratio of sleep duration/time between time to sleep and time to wake) will be derived from the Fitbit data. Sleep quality is subsequently classified into a 5 point scale where 1 is lower sleep quality and 5 is higher sleep quality [59].

**Fig. 5 Fig5:**
[figure not shown]
Data transfer and synchronisation between Fitbit Activity Tracker, Smartphone/Website, Server and the Balanced app

### User-entered self-monitoring

Participants in the user-entered group will self-monitor physical activity, sedentary, and sleep behaviour by manually entering this into the intervention platform using the My Stats section (Fig. 3). The user-entered group will be asked to self-monitor time spent in moderate-to-vigorous intensity physical activity, which is defined based on increases in breathing and heart rates and increased difficulty to carry a conversation and talk. The user-entered group will be asked to self-monitor their sedentary behaviour based on time spent sitting. The user-entered group will be asked to enter the time they went to sleep and woke up, and to self-monitor sleep quality using a 5 point scale from 1 (lowest quality) to 5 (highest quality) based on their perceived quality of their sleep.

### Randomisation

Participants will be randomised to one of the two intervention groups by a researcher not involved in participant assessments, after completion of their baseline assessment (Visit 2). The randomisation sequence will be generated using a computer-based random number generator using blocks of 4 and 6 [60]. The sequence will be generated by a researcher not involved in participant assessments and will be stored on a central database not accessible to those completing the assessments. Group allocations will be concealed in sequentially numbered opaque envelopes.

### Outcome measures

#### Primary outcome

##### Activity, sedentary and sleep behaviour

The Geneactiv is a small (36 × 30 × 12 mm, 16 g) waterproof accelerometer which has been shown to provide valid estimates of physical activity, sedentary and sleep behaviours [61, 62]. Participants will be asked to wear the Geneactiv activity monitor 24 h per day for 7 days on their non-dominant wrist and complete a written monitoring log to record the time of day that they go to bed, wake up, arrive at and leave work (if employed) and if the monitor was removed for any reason. Throughout the assessment period participants will receive text message reminders to wear the activity monitor approximately every 3 days.

The monitors will be set to collect data at 40-Hz. For data to be included in the analyses, a minimum of 5 days wear time, with at least 16 h wear per day will be required [63]. Daily time spent in sedentary, light and moderate-to-vigorous intensity physical activity (MVPA) will be determined using the Geneactiv data and the acceleration intensity thresholds developed by Hildebrand et al. [62]. In addition, the duration of specific activity types representing sedentary behaviour (i.e. sitting, standing stationary) and moderate-to-vigorous intensity physical activity (i.e. brisk walking, running) during waking hours will be quantified using the Random Forest activity classifier developed by Pavey and colleagues [64]. Geneactiv data will be used in combination with log data on time to bed and time to wake, to provide Geneactiv derived estimates of sleep onset and offset each day, sleep duration, and nightly awakenings using the R-package “GGIR” [61]. The ratio of sleep duration and time between sleep onset and offset will be used as an indicator of sleep efficiency. The within-participant standard deviation in sleep onset and offset will be calculated to provide a measure of variation in sleep-wake behaviour [65]. The primary outcomes of daily minutes of moderate and vigorous intensity physical activity, sedentary behaviour, sleep efficiency and sleep-wake variability will be averaged across days that satisfy minimum wear time criteria.

### Secondary outcomes

#### Self-reported physical activity, sitting, sleep

Self-report measures of physical activity, sitting and sleep are collected for several reasons including in the event that compliance with the accelerometer protocol is low or device malfunction. Self-reported sitting time can provide insight the domain of sitting that changes occur in and many sleep interventions report changes in self-reported sleep quality allowing comparison to these studies. The Active Australia survey will be used to assess the frequency and duration of self-reported walking for recreation and transport (combined), moderate and vigorous intensity physical activity over the last week. It has demonstrated acceptable levels of test-retest reliability (k = 0.50) and validity (k = 0.26–0.46) in population based surveys and is sensitive to detecting changes in physical activity in interventions [66–68].

The Workforce Sitting Questionnaire will be used to assess self-reported sitting time [69]. This instrument assesses the time spent sitting at work, watching TV, using a computer at home, transport and during other leisure activities on work and non-work days. It has acceptable levels of test-retest reliability (ICC = 0.46 – 0.90) and criterion validity compared to waist worn accelerometry (*r* = 0.18 – 0.46) [69].

Self-reported sleep quality will be assessed using the Pittsburgh Sleep Quality Index (PSQI) and the Behavioral Risk Factor Surveillance Sleep Module [70, 71]. The PSQI assesses the duration and quality of sleep over the previous month using 19 items that assess seven separate components of sleep, including duration, sleep latency and sleep problems. Each of the seven components are scored from zero to three and are summed to provide an overall score of sleep quality ranging from 0 to 21 where higher scores indicate poorer sleep quality. The Behavioral Risk Factor Surveillance Sleep Module contains 5 items assessing the average duration of sleep in a 24-h period, number of days in the previous month that an individual reports feeling they did not get enough rest or sleep, and unintentionally falling asleep during the day. The instrument also assesses if a person nodded off or fell asleep, even just for a brief moment, while driving in the last 30 days (yes, no, not applicable) and if they have ever been told they snore (yes, no, don’t know, unsure) [71]. Self-reported sleep timing and variation in sleep timing will be assessed using the 18 item Sleep Timing Questionnaire [72]. This instrument assesses the earliest and latest time of day a person usually goes to bed and wakes up, the usual time of day a person goes to bed and wakes up and the variation in these times on both weekends and week days. The Sleep Timing Questionnaire has demonstrated acceptable levels of test-retest reliability (*r* = 0.70), validity with accelerometery (*r* = 0.59) and sleep diary (*r* = 0.83–0.86) measures of sleep timing.

#### Depression, anxiety and stress

Physical activity, sedentary and sleep behaviours are associated with symptoms of depression, anxiety and stress and participants will complete the Depression, Anxiety and Stress Scale (DASS-21) to assess these [73–77]. Each of the 21 items in this scale asks participants to report how much each emotional experience (e.g., over reacting, feeling sad/depressed, feeling scared for no reason) statement applied to them over the previous week, using three response options from “did not apply to me at all” to “applied to me very much, or most of the time” [73, 74].

#### Health related quality of life

Health related quality of life will be assessed using the valid and reliable Centres for Disease Control Healthy Days Instrument [78–80]. This instrument assesses the self-rated health, frequency of physical and mental unhealthy days over the previous 30 days and the presence of activity limitations.

#### Mediators

##### Lifestyle behaviour habit

The 4-item automaticity subscale of self-report behavioural automaticity index will be used to assess the level of automaticity associated with physical activity, sedentary and sleep behaviours (thus 12 items in total) [81]. Example items are “Not sitting for prolonged periods is something I do without thinking”, “Consistent sleep and wake times are something I do without having to consciously remember.” Each item is assessed using a 7 point scale from Strongly Disagree to Strongly Agree. The four items for each behaviour are summed to create an overall score from 7 to 21, where higher scores indicate greater levels of automaticity. Previous research has shown that this subscale is reliable, relates to prospective behavior, and moderates between-person intention-behavior relations as theorized [81].

#### Sleep hygiene

Participants’ sleep hygiene practices will be assessed using the 13 item Sleep Hygiene Index, which assesses the frequency that participants engage in behaviours that affect sleep hygiene [82]. Each item uses a five point response scale (always, frequently, sometimes, rarely and never) which are summed to provide an overall score where higher scores indicate poorer sleep hygiene practices. The Sleep Hygiene Index has acceptable levels of internal consistency (Cronbach’s α = 0.66), test-retest reliability (*r* = 0.71), and validity compared to the Pittsburgh Sleep Quality Index (*r* = 0.37 – 0.45) and the Epworth Sleepiness Scale (*r* = 0.24).

#### Social cognitive factors

The Balanced intervention was guided by social cognitive and self-regulatory theories and items adapted from previous research are used to assess the constructs of intentions, motivation, action planning, outcome expectancies, outcome expectations, behavioural strategies, situational control, social support, and self-efficacy over a one month period [83]. The original instrument demonstrated acceptable levels of internal consistency (α = 0.63–0.79) [83]. The items were modified to align with the target behaviours of the *Balanced* intervention (e.g., regular physical activity, limit sedentary behaviour, regular sleep and wake times). A total of 11 items were used to assess these constructs for each of the three target behaviours. For each of the target behaviours a single item was used to assess intentions, motivation, action planning, situational control, social support, and self-efficacy and two items for both outcome expectancies and outcome expectations. Participants were asked to indicate their agreement with each statement using a five point scale, from Strongly Disagree to Strongly Agree.

Using five items that are answered on a five point scale, from Strongly Agree to Strongly Disagree participants reported their confidence to engage in regular physical activity, limit sedentary behaviour, and keep regular sleep and wake times, any two of these behaviours and all three of these behaviours (5 items total). Using three items that are answered on a five point scale, from Strongly Agree to Strongly Disagree participants also indicated how much they agree that their current physical activity, sedentary and sleep behaviours are a risk to their health. These items are adapted from previously used items and modified to assess the target behaviours of the intervention [49].

#### Usability, satisfaction and process evaluation

Participant perceptions of usability of the intervention platform will be assessed using the System Usability Scale, a 10 item scale that uses a 5 point response to assess agreement with each item from Strongly Agree to Strongly Disagree [84]. All items are weighted by 2.5 (including several reverse scored items) to provide an overall score from 0 to 100 where higher scores indicate greater levels of usability. Eleven items will be used to assess participant satisfaction with the intervention including the perceived usefulness of the app to self-monitor behaviours and change behaviours, the level of detailed feedback provided and the accuracy of information provided. Participants were asked to indicate their agreement with each statement using a five point scale, from Strongly Disagree to Strongly Agree. These items are similar to those used in previous studies to assess satisfaction with the intervention [28]. A randomly selected subsample of participants will also be asked to complete semi-structured interviews after completion of the study to provide information to be used as part of the process evaluation. This will include discussion on the aspects of the intervention that they believed worked well and that could be improved, information of how regularly they would like to use the app and why they did or did not use the app.

#### Engagement and use of the intervention platform

Engagement with and use of the intervention will be measured using usage statistics captured by the app database. For each behaviour and behavioural goal information is collected on the time of day and date that the entry is made and edited, the actual entry (e.g. 30 min of physical activity), and the method of entry (device-entered, user-entered). These measures are collected daily throughout the intervention period.

### Socio-demographics, Anthropometrics and cardiometabolic risk

Participants will provide information on their age, gender, years of education, occupational level, hours of work (daytime, night time, afternoon), number of days worked in previous week and average hours of work each day. Presenteeism at work over the previous 28 days will be assessed using a single item from the World Health Organization Health and Work Performance Questionnaire [85, 86]. This item asks participants to rate their performance at work on a scale of 0 to 10, where zero is the worst performance.

A research assistant blinded to group allocation will measure height, weight, waist circumference, and blood pressure with participants dressed in light clothing and without shoes. Weight (kg) will be measured on a calibrated digital scale to 0.01 kg (Biospace BSM370 Portable Automatic BMI Stadiometer, Biospace CO, Ltd., Seoul Korea). Weight will be measured twice if the two values are within 0.1 kg. If measurements vary by more than 0.1 kg a third measurement will be taken and the average of the two measures that are within 0.1 kg will be recorded. Height (cm) will be measured to 0.1 cm using a stadiometer (Biospace BSM370 Portable Automatic BMI Stadiometer, Biospace CO, Ltd., Seoul, Korea). Two measures of height will be taken and if values are not within 0.3 cm a third measure will be taken. The average of the two height measures within 0.3 cm will be taken. Waist circumference (cm) will be measured at the umbilicus (Seca 203, Seca Gmph & Co. Hamburg, Germany). Two measures will be taken, if these measures are not within 0.5 cm a third measure of waist circumference will be taken. The average of the two waist circumference measures within 0.5 cm will be taken [87].

Blood pressure and resting heart rate will be taken using a digital sphygmomanometer (Omron HEM-7320, Omron Healthcare, Co., Ltd., Kyoto, Japan) after participants have been seated quietly for 5 min. Following a 5-min minimum of sitting, two measures of blood pressure will be taken with a minimum 2-min period of rest between measures. If the two measures vary by more than 10 mm Hg (systolic), 5 mm Hg (diastolic) and 5 bpm for resting heart rate, up to five additional measures will be performed until three of the measures are within these ranges. The average of the three measures within this range will be taken [87]. Measures of total cholesterol, HDL cholesterol, LDL cholesterol, triglycerides and glucose will be taken using a capillary sample of blood drawn from the finger using the Cardiochek PA (Polymer Technology Systems, Inc., Indiana, US; BHR Pharmaceuticals Ltd., Nuneaton, UK). The measures are taken non-fasted and the time of the last meal consumed will be recorded. Capillary blood samples, presenteesism, and health related quality of life are assessed at visits 2 and 8 to limit participant burden associated with collecting capillary blood samples and due to the recall periods used in the presenteeism and health related quality of life measures.

Diet is also assessed in order to account for the effects of any changes in diet on physical activity and sleep and also measures of cardiometabolic risk [88–90]. Dietary items will assess consumption of fruit, vegetables, takeaway food consumption, drinks containing caffeine, and drinks containing alcohol. Fruit and vegetable consumption is assessed by the number of serves of these foods usually eaten each day. Consumption of takeaway food (pies, pastries, fried foods, hot chips, or takeaway meals) is assessed as the number of times per week. These items are based on an existing instrument that has demonstrated acceptable levels of validity compared to a 4 day food diary (*r* = 0.32 – 0.55) [91]. Alcohol and caffeine consumption are assessed using 4 items to assess the number of days in the last week that drinks containing alcohol and caffeine were consumed, and the number of drinks consumed on each day. These latter items are adapted from existing instrument used to assess risky alcohol consumption [92].

### Power and sample size

A statistician independent of the research team performed the power and sample size calculations were based on detecting between group differences in changes in physical activity (30 min difference, standard deviation = 30), sedentary behaviour (90 min difference, standard deviation =110), variation in time to sleep (30 min difference, standard deviation = 40), variation in time to wake (30 min difference, standard deviation = 35), and sleep efficiency (5 % difference, standard deviation = 5) at the end of the intervention. Assuming a correlation of 0.6 between the repeated measurements, a total sample of 48 participants will give the study 80 % power to detect a group by time interaction for each of the five primary outcome variables, using an alpha level of 0.01. Hence a minimum of 64 participants (32 per treatment arm) will be recruited into the study to allow for 35 % attrition over the study period.

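### Recruiting 64 participants covers 25 % attrition, not the stated 35 %: at 35 % about 42 remain, six short of the 48 behind the power statement

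*Protocol article*

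**What the plan says.** The Power and sample size section of the protocol article lists a difference and a standard deviation for each of five primary outcomes. It assumes a correlation of 0.6 between repeated measurements and states that "a total sample of 48 participants will give the study 80 % power to detect a group by time interaction", "using an alpha level of 0.01". The claim covers every primary outcome: "80 % power to detect a group by time interaction for each of the five primary outcome variables".

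The recruitment target is then presented, with an opening *hence*, as following from the 48: "a minimum of 64 participants (32 per treatment arm) will be recruited into the study to allow for 35 % attrition".

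The abstract and the Participant recruitment section repeat 64. The article gives no other attrition rate and no other inflation rule.

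**The concern.** An attrition allowance is meant to leave the required number after the expected loss. The word that opens the recruitment sentence ties 64 directly to 48, so a reader takes it that losing 35 % of 64 still leaves 48. It does not.

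At stake is the reassurance that the sentence gives. A sponsor, funder or ethics committee reading it would believe that the trial can lose about 22 people (64 × 0.35 = 22.4) and still have the sample behind its power statement. It can lose only 16 (64 − 48). In a trial of this size, six participants is a material difference.

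**Working it through.** **Inputs, all from Power and sample size:** required total N = 48; attrition d = 0.35; recruitment target R = 64 (32 per arm).

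**Step 1. Try to reproduce the plan's 64.**
- Divide by the retained fraction, N/(1 − d): 48/0.65 = 73.8, so 74 (37 per arm). This is not 64.
- Add the percentage to N, N × (1 + d): 48 × 1.35 = 64.8. This is close to 64, but rounds up to 65, or 66 with equal arms.
- Divide with d = 0.25: 48/0.75 = 64 exactly.

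So 64 does not follow from 48 and 35 % by the standard formula. It could come from adding 35 % to 48 and rounding down, or from a correct 25 % inflation with the wrong percentage printed. The second gives an exact match. The article does not show which happened.

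**Step 2. Work backwards from 64.**
- Remaining at 35 % loss: 64 × 0.65 = 41.6, about 42 in total, or 32 × 0.65 = 20.8 (about 21) per arm.
- Shortfall against 48: about 6.
- Largest loss that keeps 48: 1 − 48/64 = 25 %.
- Check on 74: 74 × 0.65 = 48.1, which keeps 48.

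**Step 3. Does power then fall below 80 %?** This needs assumptions that the article does not supply. It does not say which contrast was powered, how the standard deviations and the correlation were used, or whether the test is two-sided. As an illustration, take the outcome with the smallest standardised difference, variation in time to sleep (30/40 = 0.75 SD), with correlation 0.6 between all pairs of assessments and two-sided alpha 0.01. One contrast that gives about 80 % at 48 is baseline against the mean of the three follow-ups.

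| Data analysed | Baseline vs mean of three follow-ups | Baseline to week 9 |
|---|---|---|
| 48 complete (24 per arm) | 0.80 | 0.59 |
| 42 complete (21 per arm), dropouts discarded | 0.73 | 0.51 |
| 64 recruited, 35 % lost evenly over the three follow-ups, partial data kept | about 0.87 (0.86 with 40 df) | about 0.58 |
| 64 recruited, 35 % all lost before week 3, baseline kept | about 0.80 (0.78 with 40 df) | about 0.56 |

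The last two rows use generalised least squares with a known compound-symmetric covariance and data missing at random. Estimating the covariance, or informative dropout, would make them less favourable. The week 9 column starts at 0.59 with 48 complete, so it does not reproduce the plan's 80 %. The table shows only that the power at 35 % attrition depends on the contrast and on how dropouts' data are handled.

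**The case against.** The strongest case on the other side has three parts.

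**The mixed model uses partial data.** The Analysis section plans an intention-to-treat linear mixed model over four assessments, so someone who leaves after week 3 still contributes. A count of completers therefore understates the information available. This stands as regards power. A reader might infer that the trial must miss its 80 % at 35 % attrition, for example by falling to 73 % for variation in time to sleep. The documents do not support that. The 73 % discards all partial data and relies on a contrast that the article never names, and with partial data kept the same contrast gives roughly 0.78 to 0.87. The objection does not rescue the sentence, however. The article does not invoke partial data; it gets from 48 to 64 by an attrition allowance alone, and as an allowance for 35 % the figure is wrong.

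**Sixty-four is a minimum.** Over-recruitment is allowed. But 64 is the number presented as enough for 35 % loss, and the abstract and the Participant recruitment section give it without that qualifier.

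**The design may have been sized correctly.** If 25 % was the intended allowance, only the printed percentage is wrong. This is possible, and it is why no cause should be asserted. A reader might also infer that retention is being monitored against a wrong limit. The article contains no retention-monitoring threshold, so there is none to correct.

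**Conclusion.** The concern holds as an error of arithmetic in a stated design figure. The numbers 48, 35 % and 64 cannot all be right: 64 supports 25 % attrition, 35 % attrition leaves about 42, and 48 at 35 % attrition needs 74. This rests on nothing beyond those three figures and on reading attrition as the share of recruits who are lost.

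The effect on power is not established. It may be small or absent under the planned mixed model, and it depends on a calculation method that the article does not describe. No conclusion is drawn on whether 48 itself is right. The primary outcomes, the significance level, the allocation and the analysis model are unaffected.

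**What to change.** Restate the recruitment sentence along these lines: *64 participants (32 per arm) allows for 25 % attrition (48 completers); at 35 % attrition about 42 would complete, fewer than the 48 on which the 80 % power is based.*

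This needs no change to recruitment, which the article says began in July 2015. The cost is one sentence and a less favourable stated allowance. If the sponsor does expect 35 % attrition and wants 48 completers, the alternative is a target of 74 (37 per arm), at the cost of ten more participants.

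Do not write a power figure for 35 % attrition into the protocol from the illustration above. If one is wanted, the trial statistician should recompute it with the method that gave 48, stating the contrast and how partial data are used.
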